#### Medication review (intervention and control group)

Residents of both study groups with an ongoing antipsychotic prescription will receive a medication review by a consultant psychiatrist or geriatrician. The medication review will be based on residents’ case files and communicated as a written report including specific recommendations to the prescribing physicians.

The medication reviews will be carried out at baseline and after 3, 6, and 9 months according to national evidence-based clinical practice guidelines [23, 36], the PRISCUS-list [39] and on the basis of product information documents. The respective relevant data for the psychiatrist/geriatrician will be pseudonymised. The study coordination centre will ensure forwarding of the reviews to the prescribing physicians.

#### Information event for the nursing home staff (only intervention group)

All the staff in intervention group homes will receive relevant information about the study in a 60-min presentation. They will get particular information on the topics “antipsychotics for people with BPSD” and “PCC and non-pharmacological interventions”.

#### Training and support of “experts for person-centred care for the elderly—EPA” (only intervention group)

Based on Fossey et al. [35, 40], selected staff from the nursing homes in the intervention group will be trained and instructed to work as “experts for person-centred care (PCC) for the elderly (EPA)”. The responsibilities of the EPA will be:Identifying organisational needs for change within the institution and opportunities for developing specific aspects of carePlanning and supporting the implementation of PCC in the nursing facility.Initiating discussions with colleagues about PCC activities for specific residents.Discussion with colleagues about the medication review or contacting the prescribing physician.Advice and support of colleagues as facilitator and primary contact person for colleagues, relatives, and physicians.

The training programme for the EPA will include a 2-day initial workshop on PCC as well as continuous training and support over the 12-month study period.

The workshop will take place on two consecutive days at the respective study centre/university. An expert in PCC will present the following content:Introduction to EPCentCare.Antipsychotics in people with BPSD: list of medications, reasons for prescription, side effects, and guideline-based recommendations for use [23, 36, 41].PCC on resident level: according to Kitwood [26, 27], recognising individual residents’ needs and reasons for behaviour [40], dealing with challenging behaviour [25, 29, 40, 42, 43], and reflection of case examples.PCC on institutional level: assessing, supporting, and managing development of PCC in a nursing home [40, 41].Supervision/support programme [35].

The trained experts will be supported during the intervention period by a study nurse specialised in dementia and PCC (continuous in-house training). The supervision may be carried out individually and/or in groups in a minimum time frame of 3 to a maximum of 6 h per month and nursing home. As part of the supervision, the EPA will be supported in recognising residents’ needs [40] in implementing PCC plans, in promoting the participation of the residents in activities, and possibly in implementing environmental changes.

### Cluster-randomisation

The randomisation will be carried out on a cluster level. The randomisation list will be computer-generated by an independent external biometrician, who will be blinded to the identity of the participating organisations and residents. Nursing homes will be allocated to the intervention or control group using a balanced block randomisation, stratified by the three regions Halle (Saale), Lübeck, and Witten as well as the time point of the recruiting phase. Because of the low number of homes per stratum (*n* = 4), no further blocks within the strata are planned. This randomisation list will contain pseudonymous identification numbers for nursing homes and allocation of group A or B.

Parallel to this, responsible coordinators of the three study centres will independently determine and document the allocation (intervention group or control group) for group A and group B at study begin, without informing the external biometrician.

After completion of the baseline measurement of the corresponding recruiting phase, an independent person from the study centre in Lübeck will electronically (password-protected, encoded https portal) assign the randomisation list and nursing home data for concealed allocation [44] and will inform the nursing homes in written form. After confirmation of group allocation by the nursing homes, the assigning person will inform the coordinator of the respective study centre about the allocation results.

### Blinding

Due to the nature of the intervention, blinding of the nursing home staff and the field researchers will not be possible. However, the biostatistician, who will not be involved in conducting the study, will perform a step-wise statistical analysis blinded towards the group allocation of residents and clusters: (1) A blinded review of data without the nursing home IDs and group allocation will be carried out; depending on data structure, necessary adaptations of statistical analysis procedure will be performed. (2) Nursing home IDs and group allocation (group A or group B) are added to the data; group specific analyses will be carried out. (3) A or B will be unblinded after completion of the final analysis.

The psychiatrists/geriatricians performing the medication review are also blinded towards group allocation. Additionally, research assistants assessing the primary endpoint will be blinded towards group allocation. Data entry will be carried out without knowledge about the group allocation of the clusters.

### Measures

#### Institutional level

The description of the participating nursing homes, data on general characteristics, staff characteristics, characteristics of living environment, and living and care concept according to Palm et al. [45] will be gathered from the nursing home director before randomisation. The proportion of eligible residents receiving an antipsychotic prescription will be recorded at baseline and after 12 months.

#### Resident level

Five measurement points are scheduled in the study: baseline assessment and measurements after 3, 6, 9, and 12 months (see Table 2).

**Table 2 Tab2:** Measurements at resident level

Point of measurement		Characteristics	Measure
t_0_	Baseline^a^	Socio-demographic and clinical data	Routine data
		Quality of life	QoL-AD
		Cognition	DSS
		Agitated behaviour	CMAI
		Medication data	Routine data
		Falls and fall-related medical attention	Routine data
		Physical restraints	Routine data
t_1_ t_2_ t_3_	3, 6, and 9 months after baseline	Medication data	Routine data
		Falls and fall-related medical attention	Routine data
		Physical restraints	Routine data
		Clinical course (emergencies, hospital admissions, change in nursing care dependency, and physician contacts)	Routine data
t_4_	12 months after baseline	Quality of life	QoL-AD
		Cognition	DSS
		Agitated behaviour	CMAI
		Medication data	Routine data
		Falls and fall-related medical attention	Routine data
		Physical restraints	Routine data
		Clinical course (emergencies, hospital admissions, change in nursing care dependency, and physician contacts)	Routine data

^a^New participants after t_0_ will be assessed with the same characteristics and measures as for baseline at the subsequent measurement point

At baseline (t_0_), socio-demographic and clinical data will be assessed from all included residents and will be documented in a case report form (CRF).

Residents’ QoL will be measured at t_0_ and t_4_ using the German version [46] of a QoL instrument which is also suitable for residents with dementia. The validated instrument *Quality of life-Alzheimer’s disease—QoL-AD* [47, 48] comprises 13 items with 4-point Likert scales for self or proxy assessment (total score ranges from 13 to 52, higher scores mean higher QoL). Self-assessment will be performed by short interviews with the residents; proxy assessment will be conducted by nursing staff.

To determine a cut-off point for the QoL-AD self or proxy assessment tool, the validated *Dementia Screening Scale* (*DSS*) [49] will be used as a cognition test (internal consistency: Cronbach’s alpha = 0.94). For this purpose, nursing staff will have to evaluate different aspects of cognitive function regarding seven items with 3-point Likert scales in the domains “memory” and “orientation” over the last 4 weeks (total score ranges from 0 to 14; higher scores indicate more severe cognitive impairment). As the test will be used to decide if a QoL-AD self-assessment is feasible, we will use a cut-off point of >4 (specificity 88.8 %, sensitivity 84.2 %) [49].

Agitated behaviour as one aspect of BPSD will be assessed with a German version [50] of the *Cohen-Mansfield Agitation Inventory* (*CMAI*) [51–53] (measurement points t_0_ and t_4_). The CMAI is a caregiver rating instrument with good psychometric properties of the original version [52] and will be performed by interviewing the nursing staff. The scale consists of 25 items of agitated behaviours, each rated on a 7-point scale of frequency of occurrence over the last 2 weeks (total score ranges from 25 to 175, higher scores mean higher frequencies of manifestation).

To analyse the proportion of residents receiving an antipsychotic prescription, the median daily dose of antipsychotic drugs in chlorpromazine equivalents, and the prescription prevalence of other psychotropic drugs, the following data will be gathered: (1) prescriptions of antipsychotics (long-term and pro re nata (PRN) medication) from routine documentation at t_1_, t_2_, t_3_, and t_4_ retrospectively for the last 3 months: registered trade name or agent, dose, and prescription period; (2) current prescriptions of other psychotropic drugs (long-term and PRN medication) from routine documentation at the time point of t_1_, t_2_, t_3_, and t_4_: registered trade name or agent, and dose.

Additionally, safety and/or adverse outcome parameters like falls, fall-related fractures and sutures, fall-related medical attention, as well as the number and types of physical restraints [2] will be documented at t_1_, t_2_, t_3_, and t_4_ retrospectively for the last 3 months, using data extracted from routine documentation.

New participants during the study period will be assessed at the next measurement point after their nursing home admission: socio-demographic and clinical data, QoL and cognition (QoL-AD, DSS), and agitated behaviour (CMAI) at this point will be regarded as baseline data of the new participant. Medication data and safety parameters since nursing home admission will also be documented retrospectively.

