### Sample size calculation

The primary endpoint of the study is the proportion of residents with at least one antipsychotic prescription after 12 months (t_4_). The following sample size estimation was performed as described in Donner & Klar [57] for the cluster-adjusted *χ*^2^-test. Based on recent prevalence data, we expect a baseline prevalence of antipsychotic prescription of 30 % [2]. Due to the measures of optimised usual care in the control group and based on the study by Fossey et al. [35], we expect the prevalence in the control group to decline slightly to 26 % after 12 months. We expect a relative risk reduction of approximately 50 % regarding antipsychotic prescription in the intervention group.

Assuming a significance level of 5 % (α = 0.05), a two-sided test for proportions, and an intra-class correlation coefficient (ICCC) of 0.05, an average cluster size of 65 nursing home residents, 15 clusters are required per group to detect a 12 % difference in proportions from 26 % of the control group at 12 months with 90 % power (β = 0.10). Presuming that six nursing homes might drop out, 36 clusters with a total of 2340 residents will be needed.

We expect 25 % of residents with early study termination due to death or moving; the other 75 % of residents of the baseline population we expect to be still living in the nursing home and to be available for the 12-month follow-up assessment. As the outcome, the analyses will focus on the group of residents living in the nursing homes after 12 months. Assuming that new residents will all be willing to participate in the study, this will not affect the sample size.

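### Newcomers' first post-allocation QoL-AD, DSS and CMAI values are defined as baseline, and for residents admitted after the 9-month visit that value is the 12-month outcome itself; harmful only if these values are used as baselines

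*Protocol article*

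**What the plan says.** The Resident level section of the protocol article sets the visit schedule: "Five measurement points are scheduled in the study: baseline assessment and measurements after 3, 6, 9, and 12 months". On quality of life it says that residents' "QoL will be measured at t_0_ and t_4_ using the German version". The CMAI has the same two time points.

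The section then gives a rule for residents who arrive later: "New participants during the study period will be assessed at the next measurement point after their nursing home admission". Their socio-demographic data, QoL-AD, DSS and CMAI "at this point will be regarded as baseline data of the new participant". Footnote a to Table 2 repeats the timing: "New participants after t_0_ will be assessed with the same characteristics and measures as for baseline at the subsequent measurement point". Neither place makes an exception for residents whose first visit is the 12-month visit.

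The Cluster-randomisation section places allocation after t0: "After completion of the baseline measurement of the corresponding recruiting phase, an independent person from the study centre" in Lübeck links the homes to the randomisation list. The Sample size calculation expects 25% "of residents with early study termination due to death or moving", assumes that all new residents will take part, and directs the analysis to those living in the homes at 12 months. Newcomers are therefore part of the analysed population.

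For secondary outcomes, the Statistical analysis section names linear or generalised linear mixed models with a random effect for cluster, and subgroup analyses by gender and cognitive status. It calls all secondary analyses exploratory and refers to Additional file 2, which is not at hand. It mentions neither a baseline covariate nor a change score.

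**The concern.** A baseline is useful because allocation cannot have influenced it. A newcomer's first assessment lacks that property. It is made up to three months after moving into a home that has already been allocated and, in the intervention group, may already be practising person-centred care. Nursing staff supply the CMAI, the DSS and the proxy QoL-AD, and the Blinding section says staff cannot be blinded. At t0 they rate before allocation; for newcomers they rate knowing it.

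For residents admitted between t3 and t4 the problem is sharper. The next visit is t4, so baseline and outcome are one measurement and the change is zero by construction.

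Three later uses would be affected:

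- A change-score or baseline-adjusted analysis of QoL-AD or CMAI would remove part of any real effect. The Trial objective section hopes that quality of life will improve or hold steady and that behavioural symptoms will not get worse, so a shrunken difference could hide real worsening as well as real benefit.
- A baseline description by arm would mix pre- and post-randomisation values.
- A cognitive-status subgroup defined by this DSS value would be formed partly after randomisation.

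**Working it through.** **Inputs from the protocol.** Visits at 0, 3, 6, 9 and 12 months; 25% turnover with full participation of newcomers; 65 residents per home; 15 homes per group required, 36 homes (2340 residents) recruited; ICC 0.05.

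**Assumptions not in the protocol.** Newcomers make up f = 0.25 of the 12-month population (full replacement); admissions are even over the year; the correlation between baseline and outcome is 0.6, with equal variances. No QoL-AD or CMAI effect or standard deviation is given, so only relative attenuation can be computed.

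**The plan's own figure.** 26% against 14%, two-sided 5%, 90% power: 232 per group. Design effect 1 + 64 × 0.05 = 4.2. Then 232 × 4.2 = 974, and 974/65 = 14.99, so 15 homes per group. 36 × 65 = 2340. The sample size reproduces and is not in question.

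**Share with baseline equal to outcome.** 0.25 × 0.25 = 0.0625: about 146 of 2340 residents, or 122 of the 1950 in 30 homes.

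**Change score, as a share of the true 12-month difference.** t0 residents (0.75) contribute the whole effect. Each quarter-year of newcomers (0.0625) contributes only what accrues after the first assessment.

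- Only the t4 entrants affected: 1 − 0.0625 = 0.94.
- Effect builds evenly in the home over 12 months: 0.75 + 0.0625 × (0.75 + 0.50 + 0.25 + 0) = 0.84.
- Newcomers show the full effect at first assessment: 0.75.

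**Baseline adjustment (ANCOVA).** The estimate is about 1 − b × D. Here b is the slope on baseline and D is the difference between arms in recorded baseline, in units of the effect. The slope mixes 0.6 for most residents with 1 for those whose baseline is their outcome: 0.9375 × 0.6 + 0.0625 × 1 = 0.625.

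- Even build-up: D = 0.0625 × (0.25 + 0.50 + 0.75 + 1) = 0.156; 1 − 0.625 × 0.156 = 0.90.
- Full effect at first assessment: D = 0.25; 1 − 0.625 × 0.25 = 0.84.
- Only t4 entrants affected: D = 0.0625; 1 − 0.625 × 0.0625 = 0.96.

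Simulation agrees: 0.90 to 0.91, 0.84 to 0.85, and 0.96.

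**12-month values without baseline.** Ratio 1.00 in all three patterns. With a true effect of zero, none of the estimates is biased by this mechanism.

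**Effect growing with the individual's own exposure.** Newcomers average half the year's exposure by t4, so even the plain 12-month comparison gives 0.75 + 0.25 × 0.5 = 0.875. The change score gives 0.75 + 0.25 × 0.375 = 0.84. The baseline rule then costs only about 3 percentage points; the rest comes from short exposure.

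**Fewer newcomers.** With 10% newcomers, change scores keep 0.98, 0.94 and 0.90 in the three patterns, and ANCOVA keeps 0.96 to 0.97 (even build-up) and 0.94 (full effect).

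**Cost of a t0-only cohort.** 0.75 × 65 = 48.75 per home; design effect 1 + 47.75 × 0.05 = 3.39. Effective residents per group: 15 × 65/4.2 = 232 against 15 × 48.75/3.39 = 216. Ratio of standard errors: √(232/216) = 1.04.

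**The case against.** The strongest reply is that the protocol contains no analysis that this rule damages. The newcomer rule governs data collection and labelling. The outcomes are defined at 12 months, the population is residents present at 12 months, and the stated model has only a cluster effect. Read that way, QoL-AD and CMAI are compared at t4 and the label does no harm. How newcomers' first values enter the models could properly be left to Additional file 2. The primary outcome has no baseline term, and no confirmatory no-harm test or margin exists to be biased. The percentages rest on a correlation, an admission pattern and an onset pattern that the documents do not give.

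All of this stands, and it limits the point. A reader might infer that the planned QoL-AD and CMAI analyses are biased towards no effect, or that every baseline-adjusted analysis would be. The documents do not support either reading. No such analysis is stated. An analysis limited to t0 residents, or one adjusting for the home's mean at t0, would escape. For newcomers admitted before t3, attenuation also requires that the intervention has already acted by the first visit. Consent and rating after allocation could shift their values in either direction.

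What the reply does not remove is the definition. It is stated in two places, without exception, and it is wrong for any use as a baseline. An analyst who follows it inherits the problem.

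**Conclusion.** The point holds in a limited, conditional form. Newcomers' first QoL-AD, DSS and CMAI values are post-randomisation measurements called baseline, and for about 6% of the 12-month population (25% newcomers, even admission) the baseline would be the outcome.

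If these values were used as individual baselines, a change-score analysis would lose roughly 6 to 25% of a real effect in either direction. An ANCOVA would lose about 10 to 16% under the two stronger onset patterns and about 4% under the mildest. These figures depend on the assumed turnover, correlation and onset, and they shrink with fewer newcomers. A baseline table by arm or a DSS-based subgroup would be contaminated in the same way if it used the newcomers' values.

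The primary outcome, an unadjusted 12-month comparison and the sample size are untouched. Since the affected outcomes are exploratory, this is a minor point.

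**What to change.** In the Resident level section and footnote a to Table 2, call the newcomers' value a first assessment. State that only t0 values, taken before randomisation, count as baseline, both in the baseline table by arm and as a covariate. State that a first assessment made at t4 is an outcome value only. If the cognitive-status subgroup uses the DSS, apply the same rule or mark the newcomers' values as post-randomisation.

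Keep the 12-month comparison of all residents, without individual baseline adjustment; this preserves the stated population. Add an analysis of QoL-AD and CMAI in the t0 cohort, adjusted for the t0 value.

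The cost is a change of wording and one extra analysis. In the t0 cohort the standard error is about 4% larger because of the smaller number of residents, before any gain from the adjustment. No data collection changes.

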#### Data for medication reviews

For residents with an antipsychotic prescription at the point of measurement (t_0_ to t_3_), we will assess all antipsychotic prescriptions during the last 3 months and provide the psychiatrist/geriatrician with this information for the medication review.

All data for medication reviews are summarised in Table 3.

**Table 3 Tab3:** Summary of data for medication reviews

Category	Variable
Medication data^a^ Long-term medication (antipsychotic drugs)	• Registered trade name or agent
	• Dosage form and regimen
	• Daily dose
	• Prescription period
	• Prescribing physician
	• Indication
PRN medication (antipsychotic drugs)	• Registered trade name or agent
	• Dosage form
	• Number of received partial dose
	• Suggested maximum dose
	• Prescription period
	• Prescribing physician
	• Case of need
Further current long-term and PRN medication	• Registered trade name or agent
	• Dose
	• Regimen
Medical care^a^	• Psychopathological reports
	• Number of physician contacts (GP, neurologist, psychiatrist, and geriatrician) over the last three months and date of the last visit
	• Body weight: current and three months before
	• Intolerance of drugs
Neuropsychiatric symptoms^a^ (over the last 2 weeks)	• Delusion
	• Hallucination
	• Aggression
	• Verbal abnormality
	• Agitation
	• Depression
	• Anxiety
	• Apathy
	• Disinhibition
	• Irritability
	• Sleep disturbances
Potential adverse effects of antipsychotic drugs^a^ (over the last 2 weeks)	• Pain
	• Aberrant motor behaviour
	• Malposition
	• Repetitive behaviour
	• Tremor
	• Somnolence
	• Delirium
Socio-demographic and clinical data^b^	• Age
	• Gender
	• Body height
	• Relevant clinical diagnoses
	• Falls

^a^Source: routine documentation of residents

^b^Source: case report form

### Process evaluation

Since we will be investigating a complex intervention, a detailed process evaluation is essential [54, 55]. Process evaluation outcomes will be collected according to a framework for cluster-randomised trials of complex interventions suggested by Grant et al. [56]. Different methods will be used for data collection alongside the study: investigators’ documentation, questionnaires on staff knowledge and self-efficacy, structured interviews, and in-depth interviews with staff, residents, and their relatives. A detailed protocol is under preparation.

